### Outcomes {12}

This trial is designed to assess differences in the specified outcome measures between the intervention and waitlist control groups at endline and follow-up. All primary and secondary outcomes will be assessed at three points: (1) Baseline, one month before the intervention; (2) Endline, one month after the intervention ends (nine months after the baseline survey); and (3) Follow-up, 9 months after the intervention ends (17 months after the baseline survey).

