#### Primary outcomes

The study’s primary outcomes (Table 4) are reductions in intimate violence, violence against children, increased father-child engagement (early stimulation), and improvements in early childhood development outcomes.

**Table 4 Tab4:** Summary of primary outcome measures

Primary outcome	Measure description	Questionnaire
Intimate partner violence (IPV): Perpetration and Victimization	Proportion of young fathers and their wives reporting perpetrating or being a victim of physical, sexual, and/or emotional IPV in the past three months. Assessed via six measures: insulted; shouted or yelled; slapped; pushed or shoved; threw something at that could hurt; physically forced unwanted sex	Male and Female caregiver
Harsh violent discipline of children	Proportion of fathers reporting they used a form of harsh/violent discipline with their child in the past month. Items include the following: shook child; shouted, yelled at, or screamed at child; spanked, hit, or slapped child on the bottom with bare hand; hit child on the bottom or elsewhere on the body with something like a belt, stick, or other hard object; hit or slapped child on the face, head, or ear; hit or slapped child on the hand, arm, or leg; beat child up, that is, hit him/her over and over as hard as you could	Male
Fathers’ increased use of child engagement (early stimulation) activities	Proportion of fathers reporting use of early learning and play activities with child (i.e., stimulation activities). Activities include the following: reading, telling stories, singing songs, taking child outside of the home, naming/counting things together, drawing things together, playing with a toy or object	Male
Early childhood development	Scores on the short-form version of the Caregiver Reported Early Development Instruments (CREDI) [46]	Male and Female

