### Sample size {14}

Sample size is based on calculations using the outcome measure of proportion of young fathers who apply positive parenting behaviors. Based on the pilot studies on REAL Fathers intervention in Uganda, and to ensure sufficient statistical power of sub-group analyses at the regional level to obtain the largest sample size necessary, we assume only 40% of the young fathers use positive parenting skills at baseline [40]. From pilot studies, the REAL Fathers intervention should improve this proportion by at least 10% (effect size on absolute scale) by the endline [40]. The sample size computation is based on the formula:$$n=\frac{[2*{\left({Z}_{\alpha /4}+{Z}_{1-\beta }\right)}^{2}*\overline{P }(1-\overline{P })]}{{({P}_{1}-{P}_{0})}^{2}}\times Deff$$where:

*n* = minimum sample size of individuals required per arm of study

*Z*_α/4_ = the critical value of the standard normal variate at significance level of α/4 (*α* is assumed to be 0.05 or 95% certainty for improvement in the four primary outcome indicators). By setting the critical *Z* value corresponding to an alpha level of 0.0125 (i.e., α/4), our sample size calculation adjusts for multiple outcome testing while maintaining an overall 5% level of statistical significance for the trial.

*Z*_1-β_ = the critical value of the standard normal distribution at a power of 1-β (assumed to be 0.80 or 80% power)

*P*_0_ = the value of positive parenting indicator at the baseline; assumed 40%

*P*_1_ = the value of positive parenting indicator at the endline; assumed to be 50%—a 10-percentage point increase based on pilot studies$$\overline{P } = \frac{{P}_{1}+{P}_{0}}{2}$$

*Deff* = clustering effect, assumed to be 2.3

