## Statistical methods

### Statistical methods for primary and secondary outcomes {20a}

The primary analysis will follow an intention-to-treat (ITT) approach, where all study participants will be analyzed according to their original randomization assignment at baseline. To evaluate intervention effects on primary and secondary outcomes, we will employ difference-in-differences (DID) regression models, which are well-suited for analyzing longitudinal data. DID estimation estimates the causal effect of the intervention by comparing changes in outcomes over time between the treatment and control groups while controlling for unobserved time-invariant characteristics, provided the parallel trends assumption and the Stable Unit Treatment Value Assumption (SUTVA) hold. To account for the complex survey design, we will incorporate random effects in the DID regression models to address clustering at the sub-county level (the unit of randomization). Additionally, clustered standard errors will be used to correct for within-individual autocorrelation and intra-cluster correlation (ICC) at the village level. Where necessary, sample survey weights will be applied to adjust for any imbalances in sub-county or district-level characteristics. As noted above in the “Sample size” section on sample size, we apply Bonferroni correction to account for multiple comparisons in primary outcomes while maintaining an overall 5% level of statistical significance for the trial.

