### Interim analyses {21b}

We will conduct interim DID regression analyses on the primary and secondary outcomes at the endline and follow-up time periods of Cohort 1 and Cohort 2. Final analyses will be conducted on the full dataset after the end of the intervention for all study cohorts (i.e., after Cohort 3 endline and again at Cohort 3 follow-up).

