## Dissemination plans {31a}

Anonymized data will be analyzed, and all results regardless of outcome will be made available by publication in peer-reviewed international journals and presentation at international scientific conferences. In addition, the REAL Fathers Consortium of researchers, implementers, and policymakers will generate on an ongoing basis short briefs and PowerPoint presentations and will ensure findings from baseline, endline, and follow-up are shared with implementing partners and community members; local, regional, and national policymakers; and global public health practitioners.

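### The claimed 5% error rate for the whole trial covers four tests done once; it is not tied to the final endline analysis, and the interim analyses of the same outcomes are neither adjusted nor labelled descriptive

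*Protocol article*

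**What the plan says.** **Error control.** Under Sample size {14}, the critical "value corresponding to an alpha level of 0.0125 (i.e., α/4), our sample size calculation adjusts for multiple outcome testing". Under Statistical methods {20a}, the authors state that "we apply Bonferroni correction to account for multiple comparisons in primary outcomes while maintaining an overall 5% level of statistical significance for the trial". The level is claimed for the trial as a whole and is not attached to a particular analysis.

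**Repeated analysis.** Under Interim analyses {21b}: "We will conduct interim DID regression analyses on the primary and secondary outcomes at the endline and follow-up time periods" of Cohorts 1 and 2. Final analyses follow at Cohort 3 endline and again at Cohort 3 follow-up. That is four interim and two final analyses of each primary outcome. The section states no alpha allocation, no testing order and no descriptive status.

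**Time points.** Outcomes {12} says that the trial assesses differences "between the intervention and waitlist control groups at endline and follow-up". However, Trial design {8} frames the null hypothesis as change from baseline to endline. Statistical methods {20a} calls the endline analysis primary and gives follow-up the role of assessing persistence.

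**Sharing.** Dissemination plans {31a} says that the consortium, on an ongoing basis, "will ensure findings from baseline, endline, and follow-up are shared with implementing partners and community members", and also with policymakers and practitioners.

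**Stopping.** Criteria for discontinuing {11b} says that the trial has no termination criteria.

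**The concern.** Bonferroni at α/4 controls familywise error at 5% for four tests, each done once. The same outcomes are to be tested again as cohorts accrue, and findings are to be shared as the programme proceeds. By Table 6, Cohort 1 endline (Oct–Nov 2024) and Cohort 2 endline (Dec 2025) both fall well before Cohort 3 endline (Nov/Dec 2026). Nothing in the text prevents a result with p < 0.0125 at an early look from being presented as a primary finding of the trial at an overall 5% level. If that is allowed, the stated error rate is wrong. What is at stake is whether a positive result reported before the final endline analysis carries the error guarantee that the protocol attaches to it.

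**Working it through.** **Inputs from the protocol.** Four primary outcomes; per-test level 0.05/4 = 0.0125; looks after Cohorts 1 and 2 and on the full set; two post-baseline time points.

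**Assumptions, not in the protocol.** Two-sided tests, with critical |z| = 2.498; cohorts of equal size; each look pools the cohorts to date, so that the statistic at look k is (x₁ + … + x_k)/√k with independent standard normal increments; correlation between outcomes 0 to 0.5; correlation between time points 0.5.

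**Step 1: the plan's own figure.** Bonferroni sum: 4 × 0.0125 = 0.050. With independent outcomes: 1 − (1 − 0.0125)⁴ = 0.049. The 5% is reproduced for four tests at one analysis.

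**Step 2: three endline looks, unadjusted.** By simulation under the null, the chance that a single outcome crosses 2.498 at one or more of three pooled looks is 2.9%, against 1.25% for one look. The bound for four outcomes is 4 × 2.92% = 11.7%.

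| Error rate, four outcomes | Correlation 0 | Correlation 0.5 |
|---|---|---|
| Final endline analysis only | 4.9% | 4.3% |
| Claim allowed at any of three pooled endline looks | 11.2% | 9.6% |
| Endline and follow-up as co-equal, final data only | 9.2% | 8.0% |
| Endline and follow-up as co-equal, all six analyses | 20% | 17% |

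The protocol does not say whether interim analyses pool cohorts. If Cohorts 1 and 2 were each analysed alone before the pooled final analysis, the second row would be about 12.8% and 11.1%.

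**Step 3: levels that would keep 0.0125 per outcome over three equal endline looks.** Pocock: about 0.0051 at every look. O'Brien–Fleming: about 0.00001, 0.0020 and 0.0118.

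**Step 4: effect on power, using the protocol's sample-size inputs as given.** These are 40% versus 50%, design effect 2.3, 10% attrition and 1872 dyads per arm. Effective number per arm: 1872 × 0.9/2.3 = 732.5. With a mean proportion of 0.45, the expected z is 0.10/√(2 × 0.45 × 0.55/732.5) = 3.85. Power is about 91% at 0.0125, about 91% at 0.0118 and about 85% at 0.0051 for the final look alone. All exceed the planned 80%.

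**Step 5: Holm.** An outcome with 80% power at 0.0125 has expected z = 2.498 + 0.842 = 3.339. If it is tested last, at 0.05, its power is Φ(3.339 − 1.960) = 92%.

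**The case against.** The strongest reply is that looking without stopping does not inflate the final test. There is no termination rule, so the four tests on the full endline data have familywise error of at most 5% whatever was examined earlier. The protocol also separates interim from final analyses and never says that an interim result will support an efficacy claim. This stands, and it limits the point: the inflation needs a claim at an interim look. But the protocol does not exclude such a claim, and it attaches the 5% to the trial without qualification.

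Three stronger readings are tempting, and the protocol does not support them.

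- **Follow-up doubles the primary tests.** Outcomes {12} names both time points, and treating them as co-equal gives 17–20% over all six analyses. But Trial design {8} and Statistical methods {20a} point to endline as primary, so these figures describe a reading that the text as a whole does not favour.
- **IPV counts as up to four tests and child development as two.** Table 4 describes IPV as "Proportion of young fathers and their wives reporting perpetrating or being a victim of physical, sexual, and/or emotional IPV in the past three months" and takes the child development score from both caregivers. That can be one composite per outcome. The protocol does not say that the reports are tested separately, and how they are combined may be left to an analysis plan that is not shown. If they are combined, this source of inflation disappears.
- **Interim arm effects will be made public and will bias later self-report.** The dissemination section speaks of endline and follow-up findings shared on an ongoing basis. It does not mention interim arm comparisons or a release before Cohort 3 is measured. Early sharing is plausible but not stated, participants are in any case unblinded after baseline, and the document gives no way to size such a bias.

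**Conclusion.** The point holds in a limited form. As written, the 5% for the trial is guaranteed only for four tests done once. If a claim may be made at any endline look, the familywise error is about 10–11%, roughly double the stated level. That figure rests on equal cohorts, pooled looks and outcome correlations of 0 to 0.5; the correlations are assumed. The final endline analysis on all three cohorts, taken alone, is at 4.3–4.9% and is not in question. The fault lies in what the protocol leaves open next to a whole-trial claim. It does not threaten the design or the sample size.

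**What to change.** In Statistical methods {20a} and Interim analyses {21b}:

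1. State that the 5% applies to one confirmatory analysis: Cohorts 1–3 pooled, at endline, with one prespecified variable for each of the four primary outcomes.
2. State that follow-up is supportive, or is tested hierarchically after endline.
3. Either label the Cohort 1 and Cohort 2 analyses descriptive, with no efficacy claim, or give them group-sequential alpha: about 0.0051 per look (Pocock), or O'Brien–Fleming with about 0.0118 at the final look. These levels assume three equal pooled endline looks and 0.0125 per outcome.
4. With a single confirmatory analysis, use Holm in place of Bonferroni. It gives the same 5% control and never less power. Bonferroni itself is valid, so this is an improvement and not a correction. If group-sequential boundaries are chosen instead, keep the 0.0125 split for which they were computed, or specify the Holm step together with the boundaries.

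The cost is a few sentences. In return, the early cohorts yield no confirmatory claim, or the final threshold becomes slightly stricter; Step 4 shows power above 80% either way on the protocol's inputs.

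Limiting the release of interim arm effects until later cohorts have been measured is optional. It is a real trade-off, because the programme is meant to be adapted between cohorts.

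### The four primary outcomes are tested by single-step Bonferroni; Holm's step-down procedure keeps the same 5% family-wise error, never rejects less, and costs one sentence

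*Protocol article*

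**What the plan says.** The protocol article, section Statistical methods for primary and secondary outcomes {20a}, says "we apply Bonferroni correction to account for multiple comparisons in primary outcomes while maintaining an overall 5% level of statistical significance for the trial" and refers back to the sample-size section. Sample size {14} takes "the critical value of the standard normal variate at significance level of α/4", sets α at 0.05 as "95% certainty for improvement in the four primary outcome indicators", and explains that "our sample size calculation adjusts for multiple outcome testing while maintaining an overall 5% level of statistical significance for the trial". Each primary outcome is therefore held to 0.0125. The article mentions no step-down rule, no ordering of the primary outcomes and no passing-on of alpha from a rejected hypothesis.

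**The concern.** Under single-step Bonferroni an outcome must reach 0.0125 even when the other three have already been shown. Nothing is gained for that strictness in terms of hypothesis tests, because a step-down test holds the same family-wise error without it.

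The setting makes this relevant. The Objectives section expects improvement in the primary outcomes, and the background describes partner violence and violent discipline as occurring together with shared causes. Several true effects at once is the situation in which single-step Bonferroni loses most. What is at stake is that a real effect on a second, third or fourth outcome, with a p-value between 0.0125 and its Holm threshold, would be reported as not shown.

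**Working it through.** **1. The plan's own figure.** 0.05/4 = 0.0125, and 4 × 0.0125 = 0.05. For four independent tests the family-wise error is 1 − (1 − 0.0125)⁴ = 0.049. The stated overall 5% is reproduced for one family of four tests.

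**2. Holm on the same family.** Order the four p-values and compare them in turn with 0.05/4 = 0.0125, 0.05/3 = 0.0167, 0.05/2 = 0.025 and 0.05, stopping at the first failure.
- *It never rejects less.* Every threshold is at least 0.0125, so any p-value at or below 0.0125 is rejected under both methods.
- *It has the same error control.* If m₀ of the four nulls are true, the first true null reached faces a threshold of at most 0.05/m₀. The chance that any of the m₀ true nulls falls below that is at most m₀ × 0.05/m₀ = 0.05, whatever the correlation.
- *The first step is unchanged.* The smallest p-value still faces 0.0125, so the chance of at least one rejection is identical.

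**3. What power to assume per outcome.** The protocol's inputs are power ("assumed to be 0.80 or 80% power"), P₀ ("the value of positive parenting indicator at the baseline; assumed 40" percent), P₁ = 50%, Deff = 2.3 and 10% attrition. Sidedness is not stated; two-sided 0.0125 is assumed here (z = 2.498). The protocol's formula gives

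2 × (2.498 + 0.842)² × 0.45 × 0.55 / 0.10² × 2.3 ≈ 1270 per arm, or 1270/0.9 ≈ 1411 with attrition.

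The planned numbers are larger, so on these inputs the power is above 80%. Power = Φ(0.10/SE − 2.498), with SE = √(2 × 0.45 × 0.55 / n_eff) and n_eff = N × 0.9/2.3:
- N = 1872: n_eff = 732.5, SE = 0.0260, 0.10/SE = 3.847, power = Φ(1.349) ≈ 91%.
- N = 2200 (the inflated target in the same section, taken here as enrolled and also losing 10%): n_eff = 860.9, SE = 0.0240, 0.10/SE = 4.170, power = Φ(1.673) ≈ 95%.

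**4. Holm against Bonferroni.** Simulation of four equally correlated two-sided z-tests, 400,000 draws per scenario. The document gives no correlation between outcomes, so 0, 0.3 and 0.5 are assumptions and the ranges below span them. Bonferroni's average power is the first column throughout.

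| Power per outcome at 0.0125 (Bonferroni) | Holm average, 1 true effect | 2 true | 3 true | 4 true | All four shown: Bonferroni → Holm |
|---|---|---|---|---|---|
| 80% | 80% | 82% | 84–85% | 88–89% | 41–56% → 69–76% |
| 91% (1872 per arm) | 91% | about 92.5% | 94% | 96–97% | 69–77% → 88–90% |
| 95% (2200 per arm) | 95% | 96% | 97% | 98–98.5% | 82–86% → about 95% |

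With one true effect the change is about 0.1 point. Holm's simulated family-wise error was at most 4.9% in every mix of true and false nulls, and no draw had a Bonferroni rejection that Holm missed.

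**The case against.** The strongest case is that nothing here is wrong. Bonferroni is valid and pre-specified, the two sections agree, and the same 0.0125 is carried into the sample-size calculation. That stands: this is lost efficiency and not an error or a contradiction.

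A reader might also infer that the expected gain is the 80% row with four true effects. The document does not support that.
- The 80% is stated for positive parenting, which the protocol lists as a secondary outcome. No effect size is given for any of the four primary outcomes, so equal power for each is an assumption.
- On the protocol's own inputs the power is about 91% or 95%. There the average gain is about 0 to 5.5 points at 1872 per arm and about 0 to 3 points at 2200.

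A reader might further infer that the trial succeeds only if all four outcomes are shown, so that the all-four column measures lost success. No section sets that criterion. The column describes one scenario.

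Finally, Bonferroni has 98.75% intervals that match its tests, and Holm has no equally simple set. For results meant for policymakers that is a fair reason to hesitate. It is a cost of presentation and does not affect error control.

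**Conclusion.** The point holds as a cheap improvement. For testing, Holm dominates the stated method: it gives the same 5% family-wise error under any dependence and never fewer rejections. The benefit is close to nil if only one effect is real. At 1872 per arm it is about 1.5 points of average power with two true effects, about 3 with three and about 5 with four. It is larger if the true power per outcome is nearer 80% and smaller at 2200 per arm. These sizes rest on two-sided tests, equal power across outcomes, correlations of 0 to 0.5, and the protocol's own Deff and attrition.

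Three limits apply. The chance of at least one positive outcome is unchanged, so the swap does not by itself justify a smaller sample. Either method holds 5% only if each primary outcome yields one p-value at one analysis. Holm does not address the multiplicity that comes from both partners' reports on partner violence and child development, from the follow-up time point, or from the interim analyses of Cohorts 1 and 2.

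**What to change.** In Statistical methods {20a}, replace the Bonferroni correction with: *Holm step-down procedure across the four primary outcomes, one p-value per outcome in the primary endline analysis, family-wise 5%*. The restriction to endline agrees with that section, which already treats the endline model as primary. Keep α/4 in Sample size {14} as the conservative planning value, so the sample size is untouched. Keep 98.75% intervals for display, with a note that an interval may include no effect for an outcome that Holm rejects.

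The cost is one sentence and that note. Because effect analyses of Cohorts 1 and 2 are planned before the final analysis, the amendment should be dated, made before the final analysis, and recorded as made without reference to interim effect results.

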**Methods:**

To assess the REAL Fathers intervention, we use a cluster-randomized controlled trial design within 48 sub-counties randomly sampled from 24 districts in six regions of Uganda. Sub-counties were randomly allocated to treatment or control arms at baseline. Study participants are fathers ages 16–25 years and their cohabitating wives whose eldest child is below the age of 3 years (*n* = 3744 couple dyads). Primary outcomes are the following: (1) reduced intimate partner violence; (2) reduced violent discipline of children; (3) increased father-child engagement and play; (4) improved early childhood development. Secondary outcomes include the following: (1) father’s knowledge of and (2) attitudes towards positive parenting and discipline; (3) father’s use of positive parenting and discipline; (4) father’s use of emotional engagement with child; (5) couple communication and conflict resolution; (6) gender equitable household and caregiving decision-making and behaviors; (7) father engagement in child health-promoting activities; (8) improved knowledge of family planning methods; (9) reduced unmet need for family planning; (10) reduced problem alcohol use; and (11) supportive community norms for father-child engagement and play. Longitudinal survey data will be collected by trained enumerators using KoboCollect in six local languages at three time points: one month before the intervention (baseline); one month after the intervention (endline); and nine months after the intervention (follow-up). Intervention effects on primary and secondary outcomes will be assessed using difference-in-differences (DiD) mixed-effects models that account for the clustered design.

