Since all trial outcomes are binary, we will use mixed-effects logistic regression models for the primary endline analysis. As a supplementary analysis, we will estimate causal effects in terms of risk differences using mixed-effects linear models, implemented via the *xtdidregress* and *xtreg* commands in Stata. Individual-level observations will be analyzed rather than cluster-averaged data, following methodologies outlined by Hussey & Hughes (2007) and Baio et al. (2015)) [54, 55]. Let $${Y}_{ijk}$$ denote an outcome of individual *i* from *j*th subcounty and *k*th region measured at time period *t*, and modelled as:$$logit(P({Y}_{ijkt}=1)={\beta }_{j}+\lambda {G}_{i}+\alpha {T}_{i}+\gamma {(GT)}_{i}$$where $${\beta }_{j}$$ is the random effects term for the sub-counties (with $${\beta }_{j} \sim N\left(0,{\tau }_{\beta }^{2}\right)$$.); $$\lambda$$ is fixed effect of randomization group (G_*i*_ = 1, if exposed to intervention; and G_*i*_ = 0, otherwise); $$\alpha$$ is a fixed effect of time (T_i_ = 0 if baseline, T_i_ = 1 if endline), and $$\gamma$$ is an interaction effect of time and group. Predicted margins will be used to compute the average causal effect or equivalently the ITT estimand.

For follow-up analysis, we will implement a three-time-point panel model to assess the persistence of treatment effects nine months post-intervention closure. Additionally, a two-time-point analysis (comparing endline and follow-up) will be conducted as a sensitivity analysis to evaluate short-termeffects.

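### The primary endline model is logistic because every outcome is said to be binary, but the fourth primary outcome is a CREDI score with no cut-off

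*Protocol article*

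**What the plan says.** The abstract lists four primary outcomes, the last being "4) improved early childhood development". Table 4, under Primary outcomes, gives each one a measure. Three are proportions; violent discipline, for example, is "Proportion of fathers reporting they used a form of harsh/violent discipline with their child in the past month". The fourth is different: "Scores on the short-form version of the Caregiver Reported Early Development Instruments (CREDI" short form is scored, and the table names no threshold, category or proportion.

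The statistical methods section {20a} then states: "Since all trial outcomes are binary, we will use mixed-effects logistic regression models for the primary endline analysis". The equation that follows models the logit of P(Y = 1), with a sub-county random effect and terms for group, time and their interaction. The only linear model in that section is supplementary: "we will estimate causal effects in terms of risk differences using mixed-effects linear models".

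The Sample size section {14} splits alpha over the four primary outcomes, with a critical value "corresponding to an alpha level of 0.0125 (i.e., α/4"), and {20a} repeats that a Bonferroni correction applies to them.

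**The concern.** The choice of model is derived from a premise that Table 4 contradicts. A logistic model for a 0/1 outcome cannot take a score, and the linear model does not fill the gap, because it is supplementary and aims at a risk difference, which also needs a 0/1 outcome. An analyst who follows {20a} has to cut the CREDI score at a point that the protocol does not define. An analyst who follows Table 4 has to leave {20a}.

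At stake is the child-development question, which the Discussion singles out as rarely examined in violence-prevention trials. Cutting a score usually discards information. A cut-off or model still open for a confirmatory outcome also leaves room for choice once data exist. Table 6 schedules Cohort 1 endline for October–November 2024, the protocol version is dated 10 December 2024, and {21b} plans interim analyses of the primary outcomes in Cohorts 1 and 2.

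**Working it through.** **1. The passages side by side**

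| Primary outcome (Table 4) | Defined as | Fits logit P(Y = 1)? |
|---|---|---|
| Intimate partner violence | proportion | yes |
| Violent discipline | proportion | yes |
| Father-child engagement | proportion | yes |
| Early childhood development | CREDI scores | no |

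Table 5 describes the secondary outcomes as proportions, so CREDI is the one exception to the statement in {20a}.

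**2. The plan's own sample size**

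The article gives no figure for CREDI. Its figure of 1,872 dyads per arm comes from one proportion, positive parenting, rising from 40% to 50%, with power "assumed to be 0.80 or 80% power", a design effect of 2.3 and 10% attrition. The stated formula is n = 2(Z + Z_power)² × P̄(1 − P̄)/(P1 − P0)² × Deff, with P̄ = 0.45. The critical value is described only as "the critical value of the standard normal variate at significance level of α/4", so both readings were tried:

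- One tail of 0.0125 (Z = 2.241): 470.5 × 2.3 = 1,082; divided by 0.9, this is 1,202.
- Two-sided 0.0125 (Z = 2.498): 552.0 × 2.3 = 1,270; divided by 0.9, this is 1,411.

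Neither gives 1,872. That is a separate matter and does not bear on this point, so 1,872 is taken as stated below.

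**3. Information kept if the score is cut**

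Assumption: the score is roughly normal and the effect is a small shift. With a share q on one side of the cut, the efficiency relative to comparing means is φ(z_q)² / [q(1 − q)].

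| Cut | Calculation | Kept | Sample multiplier |
|---|---|---|---|
| 50% | 0.3989² / 0.25 | 0.637 | 1.57 |
| 20% | 0.2800² / 0.16 | 0.490 | 2.04 |
| 10% | 0.1755² / 0.09 | 0.342 | 2.92 |

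These cuts are illustrative, since the article names none.

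The shape of the score matters. At a median cut, the same large-sample comparison keeps 0.82 for a logistic-shaped score (18% lost) and 0.33 for a uniform one (67% lost). For a sharply peaked double-exponential shape the ratio is 2.0, so a median cut would lose nothing against a comparison of means.

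**4. What the trial could detect on the continuous score**

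Assumptions: two-sided alpha 0.0125, 80% power, 1,872 per arm, 10% attrition, and the design effect of 2.3 borrowed from positive parenting.

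- Effective n per arm = 1,872 × 0.9 / 2.3 = 732.5.
- Detectable difference = (2.498 + 0.842) × √(2/732.5) = 0.174 SD.

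At that difference, power after a cut is Φ(3.339 × √efficiency − 2.498): about 57% at a median cut, 44% at a 20% cut and 29% at a 10% cut, against 80% for the continuous score.

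The Sample size section ends with a target of 2,200 per arm. With that figure, effective n = 2,200 × 0.9 / 2.3 = 860.9, and the detectable difference is 3.339 × √(2/860.9) = 0.161 SD.

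Both differences are for a comparison of endline means. A simple difference-in-differences multiplies them by √[2(1 − r)], where r is the baseline–endline correlation. They are unchanged at r = 0.5, larger below it and smaller above it. The article gives no r for CREDI.

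**The case against.** The strongest reply is that this is a matter for the analysis plan. Section {31c} says that indicators and an analysis plan will be registered and published before analysis starts, and a CREDI threshold or a separate model could be set there. Other outcomes also lack a full scoring rule: Table 4 lists seven father-child activities without saying how many count as use. This stands as far as it goes, and the missing cut-off alone would be no finding. It does not remove the contradiction, because the article is not silent: it says that all outcomes are binary and fixes a model on that ground.

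Three stronger readings are tempting, and the documents do not support them:

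- **That at least a third of the information will be lost.** This holds for a roughly normal score only. The loss is also measured against a continuous analysis that the trial was never powered for, so no stated CREDI power is being given up.
- **That the model will be chosen after seeing the data.** Given {31c}, this is a risk and not an established fact.
- **That the sample size treats all four primary outcomes as proportions.** It uses one positive-parenting proportion, which Table 5 lists as a secondary outcome. The four primary outcomes enter only through alpha/4.

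**Conclusion.** The point holds as an internal contradiction on one of four confirmatory outcomes. The statement in {20a} is wrong for early childhood development, and the protocol as written gives that outcome no primary model unless it is cut at an undefined point. The other three primary outcomes are unaffected.

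The contradiction needs no numerical assumption. The size of the loss does: it depends on the shape of the score and on where a cut would fall, neither of which the article gives. The detectable difference of about 0.17 SD depends on a design effect that was derived for another outcome at village level, while randomisation is by sub-county.

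**What to change.** - **Wording.** In {20a}, say that all outcomes except the CREDI score are binary. This keeps the statement correct for the secondary outcomes too.
- **Model.** Name as the primary analysis of the CREDI score a linear mixed-effects difference-in-differences model of the continuous score, with the same sub-county random effect and village-clustered standard errors, tested at alpha 0.0125. This stays within the plan's own framework. Adjusting for child age and baseline score is an optional gain in precision and is not needed to resolve the conflict.
- **Respondent.** Table 4 collects CREDI from fathers and mothers, so the model line, or the analysis plan, should say whose report is analysed.
- **Detectable difference.** State the standardised difference that the trial can detect, with the sample size per arm, attrition, design effect and, for difference-in-differences, the assumed baseline–endline correlation.

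A pre-specified, justified cut-off would also remove the contradiction, but probably at a cost in power.

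The cost is a few sentences and one model line, with no change to data collection. The one input to be found is a design effect or intra-cluster correlation for CREDI, which the article does not give; until then 2.3 should be labelled as borrowed. The change should be dated, with a note of which cohort data had already been analysed by arm.
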